**Figure 1. F1:**
[figure not shown]
Flowchart depicting study protocol. POCUS: point-of-care ultrasound.

Subjects will be observed for a period of 1 month to determine whether they have returned for a repeat consultation for the same reason, and if so, to check the degree of alignment of the final diagnosis with the initial care. Only in cases where the process is not resolved can the patient be monitored for the next 6 months.

### Statistical Analysis

A descriptive analysis will be carried out including proportions, measures of central tendency, and measures of dispersion, according to the nature of the variables (quantitative variables expressed as mean and SD and qualitative variables as a percentage). The analysis will include description and statistical analysis to identify any significant differences between men and women.

Comparison of the variables of interest and the stratification and potentially confounding variables at the start of the study will be carried out in both groups. The baseline values of the study variables will be tested for their homogeneity between the two groups (Student *t*-tests and chi-square tests, depending on the nature of the variables). There will also be a normality check for variables such as length of stay and those that require it.

The emergency department length of stay will be compared using a Student *t* test for independent samples, and a multiple linear regression model will be applied to adjust for potential confounding factors. The number of plain radiographs and complementary imaging studies in the Radiology Department will be analyzed using Poisson or logistic regression models, as appropriate. To account for multiple hypothesis testing, a Holm-Bonferroni correction will be applied.

The possible existence of potential confounding factors or the interaction of other variables in the relationship between the proposed intervention and the outcome variables will be assessed using logistic regression models. For continuous variables, it will be assessed by multiple linear regression.

In all cases, a statistical significance of 5% (*P*<.05) is required. The data will be processed and analyzed with SPSS (version 25.0; IBM Corp).

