In the diagnosis of nephrourological pathology such as renal colic, clinical ultrasound is a good diagnostic tool with a high level of accuracy in detecting urinary tract dilation [12]. These patients may also benefit from an improved level of risk stratification [13]. An observational study has already validated an algorithm for patients with flank pain in the examination and detection of urolithiasis [14]. The use of computed tomography for this pathology has increased, so a review was carried out to compare ultrasound as an alternative and safe test for the patient, which concluded that there is sufficient evidence to determine a more rational algorithm for the management of renal colic [15]. The use of POCUS was also found to be associated with a shorter emergency department stay compared to computed tomography [16].

In the emergency department, the length of stay is determined by many factors, such as the patient’s age, the need for laboratory tests, or referral for consultation, but another factor to be taken into account is the need for ultrasound in abdominal pain [17]. In view of the limited time in the emergency department, ultrasound examination by family doctors is regarded as helping to improve the overall diagnosis and treatment of patients [18]. A recent study from October 2022 also analyzed the effect of POCUS in the initial assessment of patients with acute abdominal pain by evaluating the diagnosis and the decrease in patient waiting time without significant changes in the cost of the service [19].

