**Inclusion criteria**
Patients treated at the Emergency Department of Riotinto Hospital during the study and follow-up periodPatients presenting with acute de novo abdominal pain, defined as a clinical condition causing pain localized by the patient between the thorax and the pelvis. Additionally, patients must not have been admitted for the same condition in the previous 3 months.Age ≥18 yearsPatients with sufficient capacity to provide written informed consentExperimental group: Patients will be attended by physicians from the Emergency Department of Riotinto Hospital and by professionals with demonstrated training in clinical ultrasoundControl group: Patients will be attended by physicians from the Emergency Department of Riotinto Hospital and by professionals without demonstrated training in clinical ultrasound

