**Exclusion criteria**
Patients with readmission due to abdominal painPatients who leave the emergency department before completing carePatients followed in other regional health systems or private health carePregnant womenPatients with morbid obesityPatients with severe mental illnessPatients whose clinical severity prevents obtaining informed consentIntercurrent illness that makes participation impossible

The reasons for study discontinuation are as follows: (1) patient withdrawal, (2) withdrawal of informed consent, (3) death, (4) protocol violation, and (5) intercurrent illness preventing continued participation.

Informed consent will be obtained by the attending physician at the time of patient evaluation, prior to any study-related procedures.

For the sample size calculation, emergency department length of stay was used as the primary variable, as it is the only parameter that has been studied to date (19). A 25% reduction in the mean length of stay is expected in the intervention group compared with the control group. According to the multicenter trial [30], the mean length of stay for patients with nontraumatic abdominal pain in the emergency department was 5.2 (SD 3) hours. Assuming a 25% reduction (1.3 h) in the intervention group, with a 2-sided significance level of 0.05 and a power of 80%, and applying a Student *t*-test for independent samples, a minimum of 84 patients per group is required. Considering an anticipated 15% attrition rate, the total number of participants to be recruited will be 194 patients (97 per group).

There will be no randomization of the sample, as the 2 groups will receive the same care as normal for their pathology; however, in the experimental group, the intervention (clinical ultrasound) will also be carried out to test its effectiveness and assess whether it improves the quality of care. It is important to consider that clinical ultrasound is not a regulated ultrasound, but rather a response to a clinical question; therefore, it is not a complex intervention, and with the usual pressure of the service, it can be performed at any time of the year.

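### Two length-of-stay analyses, one unadjusted and one adjusted, are planned for a nonrandomised comparison without saying which one governs the conclusion

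*Protocol article*

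**What the plan says.** - **Allocation.** The Methods text after the exclusion criteria states: "There will be no randomization of the sample, as the 2 groups will receive the same care as normal for their pathology". Textbox 1 separates the groups by the attending physician: control patients are those seen "by professionals without demonstrated training in clinical ultrasound", and experimental patients are seen by physicians who have that training.
- **Sizing.** "emergency department length of stay was used as the primary variable". The inputs are "the mean length of stay for patients with nontraumatic abdominal pain in the emergency department was 5.2 (SD 3) hours", a 25% reduction (1.3 h), two-sided 5% significance, 80% power and an independent-samples t test. The result is 84 per group, or 97 per group after an allowance for attrition.
- **Analysis.** In the Statistical Analysis section, "The emergency department length of stay will be compared using a Student" t test for independent samples. The same sentence adds a multiple linear regression for potential confounders, and a later paragraph repeats that confounding and interaction are assessed by linear regression for continuous variables. A Holm-Bonferroni correction and a 5% significance requirement apply.
- **Baseline comparison.** "The baseline values of the study variables will be tested for their homogeneity between the two groups", by t and chi-square tests.
- **Known drivers.** Among the determinants of length of stay, the Introduction lists the patient's age, "the need for laboratory tests, or referral for consultation".

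**The concern.** When the attending physician's training decides the group, a raw difference in mean stay mixes the effect of the scan with differences in patients, arrival times and physicians. Adjustment is therefore central to the main comparison. The plan does include it, but gives the unadjusted test first place and sizes the study on it, and it does not rank the two results. If they disagree, the team has no rule for which P value goes into the Holm procedure or which estimate is reported as the effect of bedside ultrasound. A significant t test could then become the headline even if the adjusted difference is smaller.

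The baseline significance tests add a second weakness. A nonsignificant result at this size says little about whether a prognostic factor is unbalanced enough to matter, so it may give false reassurance that the unadjusted result is safe.

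**Working it through.** **Inputs from the protocol article.** SD 3 h, difference 1.3 h, two-sided alpha 0.05, power 80%, 84 evaluable per group, 97 recruited per group.

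**Inputs assumed, because the documents do not give them.** r is the within-group correlation of a baseline factor with length of stay. d is the imbalance of that factor between groups, in SD units. R² is the variance in stay explained by the covariates.

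**1. The plan's own figure.** n = 2(1.960 + 0.842)² × 3² / 1.3² = 83.6, so 84 per group. This matches. 84 × 1.15 = 96.6 gives the stated 97. The sizing is therefore that of an unadjusted comparison.

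**2. Bias of the unadjusted difference.** Bias = r × SD × d. Its standard error is 3 × √(2/84) = 0.463 h. With no true effect, the chance of a two-sided P<.05 is:

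| r | d | Bias | Share of 1.3 h | False-positive rate |
|---|---|---|---|---|
| 0.2 | 0.2 | 0.12 h (7 min) | 9% | 5.8% |
| 0.4 | 0.3 | 0.36 h (22 min) | 28% | 12.2% |
| 0.5 | 0.5 | 0.75 h (45 min) | 58% | 36.7% |

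The bias can go in either direction, so it could imitate an effect or hide one.

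**3. What a baseline test can show.**
- A binary factor at 30% against 40%, 97 per group: z = 0.10 / √(0.35 × 0.65 × 2/97) = 1.46, P = 0.144. A ten-point imbalance passes as homogeneous.
- A continuous factor, 84 per group: an imbalance of 0.3 SD gives a significant test 49% of the time, and one of 0.2 SD 25% of the time.

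**4. Three ways of using the factor.** Simulation with 84 per group, r = 0.4, d = 0.3, no true effect, 6,000 runs:

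| Analysis | Mean bias | False-positive rate |
|---|---|---|
| Never adjusted | 0.35 h | 12.1% |
| Adjusted only if baseline P<.05 | 0.10 h | 5.8% |
| Always adjusted | 0.01 h | 5.1% |

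**5. Effect of adjustment on power.** The residual SD is 3√(1 − R²). Imbalance multiplies the variance by 1 + d²/4, which is 1.06 at d = 0.5. Power at 84 per group:

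| R² | No imbalance | d = 0.5 |
|---|---|---|
| 0 | 80.2% | 77.8% |
| 0.1 | 84.1% | 81.9% |
| 0.2 | 88.1% | 86.1% |
| 0.3 | 91.9% | 90.3% |

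Adjustment costs about two points of power at worst here, and gains power once the covariates predict stay even modestly.

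**6. Scale.** If stay is lognormal with CV 3/5.2, the SD of log stay is √ln(1 + (3/5.2)²) = 0.536. At 84 per group, power for a 25% reduction is then 93.6% on the log scale and 88.8% in raw hours with the same CV. Both exceed the planned 80%.

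**The case against.** The strongest reply is that the plan already adjusts: regression stands in the same sentence as the t test and is repeated later. Neither word order nor use in the sample size makes the t test the headline, and covariate lists and model details commonly sit in an analysis plan that is not shown here. Much of this stands. The absence of a covariate list is not the point. What remains is that this document itself fixes two analyses of one outcome, bases the size on the unadjusted one and leaves their order open.

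Some stronger readings are tempting, but the text does not support them:

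- **That the t test is the only length-of-stay analysis.** It is not; regression is planned.
- **That baseline P values select the covariates.** No such rule is stated. Even if it were applied, the simulated setting left only 0.10 h of bias and a 5.8% false-positive rate.
- **That variables arising after the scan decision will be adjusted for.** The Introduction names laboratory tests and consultation as background and Table 2 collects both, but no passage makes them covariates. The analysis text speaks of confounders at the start of the study.
- **That a specific bias is to be expected.** If the 30% against 40% factor also added 3 h, the bias would be 0.10 × 3 = 0.3 h, or 23% of 1.3 h. But 3 h is a full SD, and such a factor would explain about 23% of the variance (0.35 × 0.65 × 9 / 9). The bias would remain only if the factor were left out of the regression.
- **That analysing raw minutes is invalid.** At this size the scale is mainly a question of efficiency. A log model would also change the target from the stated difference in means to a ratio.

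**Conclusion.** The point holds as one of unstated precedence. In a nonrandomised comparison the protocol names an unadjusted and an adjusted length-of-stay analysis, sizes the study on the unadjusted one and does not say which governs. If the t test were taken as the result, the bias would be about 0.12 to 0.75 h and the false-positive rate about 6% to 37%, for r from 0.2 to 0.5 and d from 0.2 to 0.5. These ranges are assumptions. They show what could happen and do not estimate what this hospital will see. That baseline tests are a poor guide at this size follows from the planned numbers for the imbalances shown. Any gain in precision from adjustment depends on an R² that the documents do not give.

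Adjustment is necessary but not sufficient. Because the physician's training determines the group, differences between physicians in pace or test ordering cannot be fully separated from the effect of the scan by adjusting for patient covariates.

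**What to change.** In the Statistical Analysis section:

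1. Declare the regression-adjusted difference in length of stay the primary result and the one that enters the Holm-Bonferroni correction. Present the t test as descriptive.
2. Enter a short fixed set of pre-scan covariates already in Table 2 whatever their baseline P values, for example age, sex, origin, pain score and arrival time.
3. State that variables which follow the scan decision (other tests, interconsultation, radiology, discharge referral) are not adjusted for, since they may carry part of the effect.
4. Describe balance by standardised differences in place of P values.
5. Optionally, add a log or log-link model as a sensitivity analysis.
6. State residual confounding at physician level as a limitation.

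**Cost.** The change is to wording and uses variables already planned for collection. The covariates take a few degrees of freedom out of 168 evaluable patients (2 × 84), and power falls slightly if they predict stay poorly (77.8% against 80.2% in the least favourable case above). It is best settled before outcomes are analysed.

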**Methods:**

This is a pilot quasi-experimental study assessing feasibility and viability, with a nonrandomized control group, to be conducted in the Emergency Department of Hospital Comarcal de Riotinto. Adult patients (≥18 y) presenting with abdominal pain will be included. Both groups will receive standard care. In the intervention group, bedside ultrasound will be performed by trained family physicians; in the control group, ultrasound will be performed by radiologists only if deemed necessary. The primary outcome is the improvement in quality of care, assessed through a reduction in emergency department length of stay, fewer basic radiology tests requested, and diagnostic concordance. Secondary outcomes include the need for additional diagnostic studies and the appropriateness of referrals, evaluated through 1-month follow-up and reconsultation.

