## Methods

### Study Design and Setting

A quasi-experimental pilot study of feasibility and viability with a control group will be carried out at Hospital Riotinto’s Emergency Department. This center is located in the north of Huelva (Spain) and serves a population of almost 70,000 inhabitants with a high geographical distribution, as some localities are more than 80 km away from the hospital.

This study does not require registration in ClinicalTrials.gov as it does not meet the criteria for a clinical trial according to the International Committee of Medical Journal Editors and US Food and Drug Administration definitions. The project is a quasi-experimental feasibility and implementation study conducted in a real-world clinical setting, with no randomization, no experimental interventions, and no administration of investigational drugs or devices. The study aims to evaluate the impact and utility of point-of-care ultrasound performed by family physicians in emergency departments as part of standard clinical practice. Therefore, it is considered a health services research study rather than a clinical trial, and formal registration is not applicable.

The implementation of bedside clinical ultrasound performed by family physicians in the emergency department is hypothesized to reduce patient length of stay as well as the need for additional diagnostic tests, such as plain radiography or specialist-performed ultrasound, thereby improving the overall quality of patient care. The primary objective is to analyze the impact of this intervention on length of stay, the number of simple radiology tests requested, and the necessity for further examinations by radiodiagnostic specialists.

Specific objectives include determining the length of stay for patients receiving clinical ultrasound by family physicians compared to usual care, quantifying and comparing the number of radiographs and ultrasounds performed, and analyzing patients’ diagnostic and clinical progression over at least 1 month of follow-up. In cases where the process is not resolved, the patient can be monitored for the next 6 months. Additionally, the study aims to evaluate the number and outcomes of specialist-requested ultrasounds in relation to those performed by family physicians, identify factors influencing care quality related to patient health and sociodemographic characteristics, perform diagnostic concordance analyses, and assess patient satisfaction with the service provided.

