### Variables

The main outcome variables aligned with the study objectives include the length of stay in the emergency department (measured in minutes), the number and type of radiological tests requested, the performance of bedside ultrasound (POCUS), diagnostic concordance, and the patient’s satisfaction with the care received. Sociodemographic variables such as age, sex, and distance from home, as well as clinical and procedural variables, will also be collected.

A complete list of all study variables, including their measurement units or response categories, is provided in Table 2, grouped into thematic blocks: sociodemographic, clinical, diagnostic, and outcome variables.

**Table 2. T2:** Study protocol variables.

Block and variable		Unit or format	Notes or response options
Sociodemographic			
	Identification code	Alphanumeric	Unique ID per patient
	Gender	Categorical	Male or female or other
	Date of birth	Date (dd/mm/yyyy)	Age will be calculated
	Distance to home	Kilometers	Estimated by postal code
Clinical			
	Health problems	Free text or ICD-10^a^	Comorbidities
	Current medications	Free text	List of active treatments
	Vital signs	Numeric (per parameter)	BP^b^ (mm Hg), HR^c^ (bpm), EVA^d^, temperature (°C), SatO_2_ (%)
	Reason for consultation	Free text	Chief complaint
Care process			
	Attending doctor	Code or initials	Family physician ID
	Date or time of arrival	Time stamp	Format: dd/mm/yyyy hh:mm
	Date or time of discharge	Time stamp	Format: dd/mm/yyyy hh:mm
	Origin	Categorical	Self-referred or primary care or ambulance or other
	POCUS^e^ performed	Binary	Yes or no
	POCUS findings	Free text	Based on clinical protocol
	Other tests requested	Categorical or multiple	Blood tests or ECG^f^ or other
	Radiology test performed	Categorical	X-ray or formal ultrasound or CT^g^ or none
	Interconsultation	Binary	Yes or no; specialty if applicable
Outcome			
	Diagnosis	Free text or ICD-10	Final ED^h^ diagnosis
	Discharge referral	Categorical	Home or hospitalization or specialist or follow-up
	Length of stay	Minutes	Calculated from entry and discharge times
	Satisfaction questionnaire	Likert scale or categorical	1‐5 scale or qualitative responses
	Diagnostic concordance	Binary	Yes or no (based on follow-up or second opinion)

a
*ICD-10: International Classification of Disease, Tenth Revision.*

b BP: blood pressure.

c HR: heart rate.

d EVA: Escala Visual Analógica (VAS: visual analog scale).

e POCUS: point-of-care ultrasound.

f ECG: electrocardiogram.

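### The primary outcome is stated in conflicting ways and the Holm family is not named, so the 80% power for length of stay may not hold

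*Protocol article*

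**What the plan says.** The primary outcome is described in different ways:

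- **Abstract, Methods.** The primary outcome is quality of care, judged by shorter length of stay, "fewer basic radiology tests requested, and diagnostic concordance". The need for additional diagnostic studies is secondary.
- **Study Design and Setting, primary objective.** The items are length of stay, "the number of simple radiology tests requested, and the necessity for further examinations by radiodiagnostic specialists". Concordance appears only among the specific objectives.
- **Sample size paragraph (Methods, after Textbox 1).** Here "emergency department length of stay was used as the primary variable, as it is the only parameter that has been studied to date". The calculation is made "with a 2-sided significance level of 0.05 and a power of 80"%, with no allowance for multiplicity.
- **Variables.** Five main outcome variables are listed. They include satisfaction and "the performance of bedside ultrasound (POCUS").

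In Statistical Analysis, one paragraph gives the t test and linear regression for length of stay, then the Poisson or logistic models for plain radiographs and Radiology imaging. It ends: "To account for multiple hypothesis testing, a Holm-Bonferroni correction will be applied". Neither the family nor the number of tests is given. The section's last paragraph adds "In all cases, a statistical significance of 5"% as the requirement.

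**The concern.** Concordance is primary in the abstract but not in the Methods objective. Further imaging is secondary in the abstract but primary in the Methods objective. Condensing a longer protocol does not explain opposite classifications.

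This matters for two reasons. First, the Holm sentence follows directly on the length-of-stay test, so the natural reading puts length of stay in the family. The outcome for which the study was sized may then have to meet a threshold stricter than the 0.05 used to size it. Second, the study is not randomized, so fixing the headline outcome in advance is one of its main protections against selective reporting. With differing lists and an open family, both could be settled after the results are known.

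**Working it through.** **Inputs (sample size paragraph).** Difference 1.3 h (25% of 5.2 h), SD 3 h, two-sided alpha 0.05, power 80%, 84 evaluable and 97 recruited per group.

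**1. The plan's own figure.** By the normal approximation, n = 2(z₀.₉₇₅ + z₀.₈₀)² × SD²/Δ² = 2 × (1.960 + 0.842)² × 9/1.69 = 83.6, so 84 per group. This matches. The recruitment figure also reproduces as the article appears to have formed it: 84 × 1.15 = 96.6, so 97.

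**2. Power of the t test at each Holm threshold.** With 84 per group the noncentrality is (1.3/3) × √(84/2) = 2.81 on 166 degrees of freedom. The noncentral t distribution gives:

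| Threshold | 84 per group | 97 per group |
|---|---|---|
| 0.05 | b₁ = 79.7% | 85.1% |
| 0.05/2 | b₂ = 70.7% | 77.5% |
| 0.05/3 | b₃ = 65.2% | 72.6% |

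The normal approximation at 0.05/3 gives 66.1% and 73.4%.

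**3. How many outcomes.** The Statistical Analysis paragraph tests three: length of stay, plain radiographs and Radiology imaging. The abstract and the Methods objective also list three each. So m = 3 is the reading closest to the text.

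**4. Holm power for length of stay, m = 3.** Holm is a step-down procedure, so 0.05/3 is a floor. Length of stay is rejected

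- always, if its P value is at most 0.05/3;
- if its P value lies between 0.05/3 and 0.05/2 and at least one other outcome has P at most 0.05/3;
- if its P value lies between 0.05/2 and 0.05 and both others have already been rejected.

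For independent outcomes, with q₃ and q₂ the power of each other outcome at 0.05/3 and 0.05/2:

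Power = b₃ + (b₂ − b₃) × u + (b₁ − b₂) × v, where u = 1 − (1 − q₃)² and v = q₂² − (q₂ − q₃)².

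The article gives no figures for the other outcomes, so their power at 0.05 is assumed:

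| Power of each other outcome | q₃ | q₂ | u | v | Length of stay, 84 per group | 97 per group |
|---|---|---|---|---|---|---|
| No effect | 0.008 | 0.013 | 0.017 | 0.000 | 65.3% | 72.7% |
| 50% | 0.332 | 0.389 | 0.554 | 0.148 | 69.6% | 76.5% |
| 80% | 0.658 | 0.712 | 0.883 | 0.504 | 74.6% | 80.8% |
| 90% | 0.802 | 0.841 | 0.961 | 0.706 | 76.9% | 82.7% |

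For example, at 80%: 0.652 + 0.0556 × 0.883 + 0.0900 × 0.504 = 0.746. A simulation with a correlation of 0.5 between the outcomes gave values about 1.6 points lower than under independence (68.7% against 70.3%, and 73.7% against 75.3%, both by normal approximation).

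**5. What 80% at the floor would take.** At 0.05/3, 2 × (2.394 + 0.842)² × 9/1.69 = 111.5, so 112 evaluable per group (113 by noncentral t). With 84 per group, the difference detectable with 80% power at 0.05/3 is 1.51 h rather than 1.3 h.

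**The case against.** The strongest reply is that the article never says length of stay is in the Holm family. The sample size paragraph calls it the primary variable. If it is tested at 0.05 and Holm covers only the rest, the 80% stands. Defining the family is also commonly left to an analysis plan, which is not shown. This stands in part: the power loss is conditional and should be reported so. It does not remove the point, because the article itself contradicts its own ranking of outcomes, and no passage takes length of stay out of the correction.

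Three stronger readings are tempting, and the article does not support them.

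- A reader might count the five main outcome variables and test length of stay at 0.05/5, where power is 58.1%. Those five are not called primary outcomes or a testing family. One of them, whether bedside ultrasound was performed, defines the groups and is not a between-group hypothesis.
- A reader might infer that the 5% sentence contradicts Holm and leaves familywise error uncontrolled. It can equally mean Holm-adjusted P values compared with 0.05. It is ambiguous rather than contradictory.
- A reader might take 65% as the power. It is the floor. Length of stay also comes from arrival and discharge times, so loss at the one-month follow-up need not remove it. With all 97 per group evaluable and the other outcomes at 80% power or more, Holm power slightly exceeds 80%.

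The article calls the study a pilot and exploratory, which lowers the stakes. However, it gives a formal power calculation and formal tests, so the mismatch still counts. The estimate of the difference and its unadjusted interval do not depend on the Holm family.

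**Conclusion.** The point holds in conditional form. The primary outcome is stated inconsistently, and the Holm family is undefined in a paragraph that includes the length-of-stay test. If length of stay is one of three outcomes in the family, then at the planned 84 evaluable per group its power is about 65% at worst and roughly 70 to 77% if the other two have 50 to 90% power each. It stays below 80% at that size whatever the other outcomes do, since 79.7% is the ceiling. If all 97 per group are evaluable, the floor is about 73%.

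These figures rest on the article's 1.3 h and SD 3 h, on m = 3 inferred from the paragraph, on assumed power for the other outcomes, and on independence between outcomes. The 84 per group is not an arithmetic error. The fault is the mismatch between the alpha used for sizing and a multiplicity rule of unstated scope.

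**What to change.** Name emergency department length of stay as the single primary outcome in the abstract, the primary objective, the sample size paragraph and the Variables section, tested at two-sided 0.05. The multiplicity plan then gives no reason to change 84, 97 or 194.

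List one secondary family (plain radiographs, Radiology imaging, concordance, satisfaction) and apply Holm within it only. State that the 5% threshold for that family refers to Holm-adjusted P values. Remove performance of bedside ultrasound from the outcomes and keep it as a process variable.

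If several primary outcomes are preferred, that is also a valid design. They should then be listed identically everywhere, and the length-of-stay power restated for three outcomes as about 65% to below 80% at 84 per group.

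The cost is no extra patients and no change in procedures. Outcomes that the abstract calls primary become secondary. The article sends significant modifications to the ethics committee, so the change may need notification. Recruitment was ongoing when the article was written, so the change should be made and dated before any outcome data are analysed.
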